#### Inclusion criteria

Pregnant women between 12 and 18 weeks of gestation with viable intrauterine pregnancy.

#### Exclusion criteria

History of severe psychiatric or substance abuse disorder requiring medical treatment or presence of fetal chromosomal/structural abnormality.

#### Recruitment pathway

The participant recruitment pathway and the follow-up during pregnancy are described in figure 1.

**Figure 1 F1:**
[figure not shown]
Overview of the study and timeline. EPDS,
Edinburgh Postnatal Depression Score; GAD7, Generalised Anxiety
Disorder 7; IES-R, Impact Event Scale-R.

### Intervention

The intervention is a web-based psychosocial peer-to-peer support during pregnancy. It will be administered using WhatsApp and WeChat APP to contact pregnant women and provide psychosocial support over chat, call and video function.

The evidence-based eHealth peer-to-peer psychosocial intervention ‘Thinking Healthy’ will be tested in this RCT. In line with the WHO’s mental health gap (mhGAP) Intervention Guide, ‘Thinking Healthy’ is used to identify and manage perinatal mental health conditions (distress, symptoms of depression and anxiety) in non-specialised psychosocial support setting.^37^ ‘Thinking Healthy’ includes guidance on evidence-based interventions to identify and manage a number of priority mental health conditions. ‘Thinking Healthy’ has been widely used in low and low-middle income countries with limited mental health professionals.^38^ One of such priority conditions is perinatal depression. ‘Thinking Healthy’*”* also uses strategies (plans and activities) taken from iCBT^39^ to bring about a change in the mothers’ symptoms and functioning. The training does not turn the non-specialised health workers or trained peers into cognitive behavioural therapists—it only allows them to apply these strategies in their day-to-day work with women in the perinatal period. Non-specialised health workers or trained peers can practice ‘Thinking Healthy’.^40^ The research team provides support for the non-specialised healthcare workers and peers. In our RCT, the web-based psychological support will be provided by trained peers using diverse web-based tools, including video calls, chat messaging and voice calls for both women and their partners.

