### Sample size and power calculation

The sample size was calculated using an online sample size calculator (CinCalc.com) to detect a 20% difference in mean EPDS scores between the intervention versus control groups with a 80% power and an alpha of 0.05 in each study location.^50^ EPDS scores show a normal distribution with a mean of 12.5 and SD of 4.0.^51^ A difference of 20% in the primary outcome is of clinical relevance with regards to the symptomatology of PPD.^52^ Based on this, the calculated sample size is 40 participants in each arm (intervention/control) of the study in each study location (n=80 participants per city). Taking into account and possible dropouts, we estimated a required sample size of 100 participants for each city (study location). The same principle will be applied if any additional study locations are added to this multicentre RCT.

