### Statistical methods

Data will be analysed per protocol using an intention-to treat method. Average EPDS, GAD7 and IES-R scores will be compared between the intervention and control groups and across time points (prenatal and postnatal), using independent sample t-tests. Differences in proportions will be assessed using χ^2^ test. The non-normally distributed continuous variables will be analysed with the Mann-Whitney U test, and the results of the intervention will be analysed by Cohen’s effect size. Multiple imputations will be used for missing data. The variables used in the imputation mode will be previous EPDS score, education level and parity. All patients’ demographic data, retrieved from web survey, will be analysed by descriptive (mean, median and range) statistics. For categorical variables, absolute frequency, percentages and/or proportions will be calculated. χ^2^ or Fisher’s exact test will be used for comparison between groups. For the primary outcome measure, a two-sided p value of <0.05 will be considered significant. Subgroup analyses will be performed for several subgroups of EPDS scores. Spearman’s correlation test will be used to test the correlation between maternal antenatal mental health characteristics assessed by EPDS, GAD7 and IES-R at <34–36 weeks and at 6 weeks postpartum.

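### Peers deliver support in one arm only; if a peer supports several women, the planned t-test and sample size make no allowance for correlation within peer

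*Protocol article*

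**What the plan says.** Under Recruitment and blinding, the protocol article randomises individual women. Under Trial design and setting and under Intervention, trained peers deliver the support by chat, voice and video: "In our RCT, the web-based psychological support will be provided by trained peers using diverse web-based tools". Under Control group, the other arm receives standard care at maternity clinics, with no study peer.

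Under Statistical methods, the means of all three scales (EPDS, GAD7, IES-R) "will be compared between the intervention and control groups and across time points (prenatal and postnatal), using independent sample t-tests", and for the primary outcome "a two-sided p value of <0.05 will be considered significant".

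Under Sample size and power calculation, each city is sized separately "to detect a 20% difference in mean EPDS scores between the intervention versus control groups with a 80% power and an alpha of 0.05". The assumption is that "EPDS scores show a normal distribution with a mean of 12.5 and SD of 4.0", and "the calculated sample size is 40 participants in each arm". No design effect enters. The target is then raised from 80 to 100 per city for dropouts.

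Peer does not appear as a factor under Statistical methods, Analysis plan or Confounders. The article gives no number of peers, no caseload, no pairing rule and no ICC.

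**The concern.** When one provider treats several participants, the provider's skill and style can make their outcomes more alike than those of participants who have different providers. Here this could arise in the intervention arm only, which makes the design partially nested. An independent-samples t-test takes the variance of the intervention mean as SD²/n. With correlated scores the variance is larger, by a factor that grows with caseload and ICC.

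Three things would then be at stake: confidence intervals that are too narrow, a type I error above the nominal 5%, and power below the planned 80%. Identity of the peer also has to be captured while support is being delivered. If it is not, the correlation can neither be modelled afterwards nor shown to be negligible.

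This is a challenge to a method that the article fixes, namely the test and the basis of the sample size. It is not a complaint that detail has been left to a fuller document.

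**Working it through.** **Inputs from the protocol article (Sample size and power calculation; Statistical methods).** Mean 12.5, SD 4.0, difference 20% × 12.5 = 2.5 points, two-sided alpha 0.05, power 80%, 40 evaluable women per arm per city.

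**Inputs that must be assumed.** Women per peer, m: 1 to 20. ICC: 0.02 to 0.05. Neither is in the article.

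**Step 1. Reproduce the stated size.**
n per arm = 2 × [SD × (z₀.₉₇₅ + z₀.₈₀) / difference]² = 2 × [4.0 × 2.8016 / 2.5]² = 40.19.
The stated 40 agrees apart from rounding down. At 40 per arm, SE = 4.0 × √(2/40) = 0.894 and power = Φ(2.5/0.894 − 1.96) = 79.8% (78.8% from the t distribution). The enrolment target also reproduces, as 80/0.8 = 100 per city. All of this assumes independent women.

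**Step 2. Allow for peers in one arm.**
DEFF = 1 + (m − 1) × ICC, applied to the intervention arm only.
True SE = 4.0 × √[(DEFF + 1)/40].
Ratio = true SE / 0.894.
Type I error of the uncorrected test = 2 × [1 − Φ(1.96/ratio)].
Power = Φ(2.5/true SE − 1.96).
n per arm for 80% power = (1 + DEFF) × [4.0 × 2.8016 / 2.5]².

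Example, m = 10 and ICC 0.05: DEFF = 1 + 9 × 0.05 = 1.45; true SE = 4.0 × √(2.45/40) = 0.990; ratio = 0.990/0.894 = 1.107; type I error = 2 × [1 − Φ(1.771)] = 7.7%; power = Φ(2.525 − 1.96) = 71.4%.

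| Women per peer | ICC | DEFF | True SE | Ratio | Type I error (simulated) | Power | n per arm |
|---|---|---|---|---|---|---|---|
| 1 | any | 1.00 | 0.894 | 1.00 | 5.0% (4.8%) | 79.8% | 41 |
| 5 | 0.02 | 1.08 | 0.912 | 1.02 | 5.5% (5.5%) | 78.3% | 42 |
| 5 | 0.05 | 1.20 | 0.938 | 1.05 | 6.2% (6.1%) | 76.0% | 45 |
| 10 | 0.02 | 1.18 | 0.934 | 1.04 | 6.0% (6.4%) | 76.3% | 44 |
| 10 | 0.05 | 1.45 | 0.990 | 1.11 | 7.7% (7.4%) | 71.4% | 50 |
| 20 | 0.05 | 1.95 | 1.086 | 1.21 | 10.7% (10.7%) | 63.4% | 60 |

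The simulated values come from 20,000 runs of the planned t-test per row, with no mean difference and total SD held at 4.0. The last row is extreme: 20 women per peer among 40 means only two peers in a city.

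The ratio states how much larger the true SE is than the t-test's. Put the other way, at a ratio of 1.107 the t-test SE is 1 − 1/1.107 = 9.7% too small.

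**Step 3. Is there slack?** If all 50 women randomised per arm were retained, 80% power would hold up to DEFF = 50/20.09 − 1 = 1.49. That margin is already assigned to dropouts.

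**The case against.** The strongest objection is that the article never says a peer supports more than one woman. A reader might infer shared peers from the reliance on trained peers, the two support contacts per woman and the emphasis on cost-effective delivery. That inference is reasonable, but nothing in the text confirms it, and one-to-one pairing is compatible with the wording. This stands: the point has to be conditional.

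Secondly, a reader might conclude that the type I error must exceed 5%. It need not. Women are individually randomised, so if the intervention affects nobody, peers cannot make outcomes alike and the t-test keeps its level. Inflation requires peers whose effects differ but average to zero, and a wish to generalise beyond the peers used. Treating the peers as fixed is a defensible target of inference. This also stands, and it limits the claim.

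Thirdly, two contacts, with EPDS measured later at 34–36 weeks and 4–6 weeks postnatally, make a small ICC plausible. At 5 women per peer and ICC 0.02 the effect is minor. That is a fair judgement, although the article contains no figure to settle it.

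Fourthly, a random peer effect is poorly estimated when there are two to four peers in a city, which is where the problem would be worst. This stands as a limit of the remedy.

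The objection that a condensed article may leave provider effects to a fuller plan carries less weight. The article names the test and the sample-size basis, and both assume independence.

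**Conclusion.** The point holds conditionally. The test and the sample size make no allowance for peer in an arm where peers deliver the intervention. Whether this matters depends on caseload and ICC, which the article does not give. The effect is nil with one woman per peer and slight to moderate at 5 to 10 women per peer with ICC 0.02 to 0.05. It is large only in the two-peers-per-city case.

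The figures rest on 40 evaluable women per arm, equal caseloads, SD 4.0 and a normal approximation. The power column therefore describes a test with a known, correct SE. A small-sample analysis with few peers would have less power than shown.

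The documents do not support saying that the standard error is too small as a matter of fact, or that the result would rest on the skill of a few peers, because the number of peers is unknown. Nor is the stated 40 per arm an arithmetic error.

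**What to change.** State the number of peers and the caseload per city, and record a peer identifier for each intervention woman. If any peer supports more than one woman, analyse EPDS with a partially nested mixed model: a random peer effect in the intervention arm only, with small-sample degrees of freedom. Report the estimated ICC. If pairing is one-to-one, say so in one sentence and keep the t-test.

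The cost is one data field and a modified primary model. The confidence interval will be wider when peers differ. If there are very few peers, the peer variance will be imprecise and the loss of power appreciable.

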#### Intervention group

They will receive a web-based psychosocial peer-to-peer support, using ‘Thinking Healthy’ two times during pregnancy (see figure 1).

#### Control group

They will receive standard perinatal care provided at maternity clinics.

### Outcome measures

The primary outcome measure is the woman’s EPDS assessed at 34–36 weeks of gestation and at 4–6 weeks postnatally.

Secondary outcomes are GAD7 scores to assess maternal anxiety levels, IES-R score to assess PTSD and pregnancy complications, including occurrence of mental health disorders, rate of preterm birth, rate of induction of labour, rate of vaginal birth, elective caesarean sections on maternal request as well as other birth outcomes.

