**Methods and analysis:**

We plan to conduct a multicentre prospective randomised controlled trial, Mental health of Urban Mothers trial. Pregnant women living in large metropolitan cities will be recruited using internet-based application through non-profit organisations’ websites. The women who consent will be randomised to receive a web-based peer-to-peer support intervention or usual care. Data will be analysed to identify the effects of intervention on Edinburgh Postnatal Depression Score and Generalised Anxiety Disorder 7 scores as well as pregnancy outcomes. The impact of COVID-19 pandemic on maternal stress will be assesed using Impact Event Scale-R. Any differences in outcomes between cities will be addressed in subgroup analyses.

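### EPDS at two unranked visits is primary with a single unadjusted 0.05: about 7–10% false-positive risk if either visit counts, and the role of city is left open

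*Protocol article*

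**What the plan says.** All references are to the protocol article.

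- **Outcome measures:** the section names as primary "EPDS assessed at 34–36 weeks of gestation and at 4–6 weeks postnatally". It does not say which visit is the main one, or whether one or both must show an effect.
- **Statistical methods:** average scores are to be "compared between the intervention and control groups and across time points (prenatal and postnatal), using independent sample t-tests". The success threshold follows: "For the primary outcome measure, a two-sided p value of <0.05 will be considered significant". No order of testing, adjustment or joint-success rule is attached to it.
- **Sample size and power calculation:** the size is chosen for a single contrast of mean EPDS between the arms, a relative difference of 20%. Power and significance level are set city by city: "with a 80% power and an alpha of 0.05 in each study location". The inputs are given as "EPDS scores show a normal distribution with a mean of 12.5 and SD of 4.0". The result is 40 per arm and 80 per city, raised to 100 per city for dropout, and any added city is to be sized in the same way.
- **Abstract, Methods and analysis:** "Any differences in outcomes between cities will be addressed in subgroup analyses". The primary objective likewise names a single population, pregnant women in Hong Kong and Shanghai together.

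**The concern.** A threshold of 0.05 holds the trial's false-positive risk at 5% only when there is one primary test, or when a rule links several tests. Here there are two primary visits, one threshold and no rule. A significant difference at one visit and none at the other could be reported as a positive trial, and nothing in the document says otherwise.

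A second ambiguity sits on top of this. The sample-size section gives each city its own power and alpha, whereas the abstract treats the cities as subgroups of one trial. The document does not say whether the confirmatory comparison is pooled or made city by city. The number of tests that could support a positive claim is therefore not fixed, and it could grow if cities are added.

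The consequence also runs the other way. If the intention is that both visits must succeed, the error is controlled, but a calculation for one test overstates the power within a city.

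**Working it through.** **Inputs.** Mean 12.5, SD 4.0, relative difference 20%, power 80%, alpha 0.05, 40 per arm per city (Sample size and power calculation); two-sided testing (Statistical methods); two primary visits (Outcome measures). The correlation r between the two visits' test statistics is not given. It is an assumption here, shown from 0 to 0.9. Cities are taken as independent.

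**Step 1: reproduce the sample size.**
- Difference: 0.20 × 12.5 = 2.5 points.
- Per arm: n = 2 × [SD × (z₀.₉₇₅ + z₀.₈₀) / difference]² = 2 × [4.0 × (1.960 + 0.842) / 2.5]² = 40.2. This agrees with the stated 40; strict rounding up gives 41.
- A one-sided calculation gives 32 and does not match. The stated size is that of one two-sided test at 0.05, with nothing set aside for a second visit.

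**Step 2: false-positive risk if either visit suffices.** With no effect at either visit, let p(r) be the bivariate-normal probability that both |Z| values stay below 1.96. The risk is 1 − p(r) for one comparison at two visits, and 1 − p(r)² if two cities are tested separately and any success counts.

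| r | Two tests: two visits, pooled or in one city | Four tests: two visits in each of two cities |
|---|---|---|
| 0 | 9.75% | 18.5% |
| 0.5 | 9.1% | 17.3% |
| 0.8 | 7.8% | 15.0% |
| 0.9 | 7.0% | 13.6% |

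Check at r = 0: 1 − 0.95² = 9.75%, and 1 − 0.95⁴ = 18.5%.

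**Step 3: power if both visits must succeed, within one city.**
- Expected test statistic at 40 per arm: 2.5 / (4.0 × √(2/40)) = 2.795.
- Power at one visit: Φ(2.795 − 1.960) = 79.8%.
- Power at both visits, with the same 2.5-point effect at each: 63.7% at r = 0 (0.798²), 66% at r = 0.3, 68% at r = 0.5, 71% at r = 0.7 and 75% at r = 0.9.
- With no effect at either visit, the false-positive risk under this rule is 0.25% at r = 0 and 3.0% at r = 0.9. It cannot exceed 5%, because each visit must pass its own 5% test.

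**Step 4: pooled comparison.** With 80 evaluable per arm over two cities, the expected statistic is 2.5 / (4.0 × √(2/80)) = 3.953. Power for one test at 0.05 is about 97.6% (t-test).

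**The case against.** There are four fair objections.

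1. **City-by-city testing is not established.** A reader might infer from the sample-size wording that each city is a separate primary test, so that the trial's error is simply 17% or more. The document does not support that. The words about each location describe how the trial was sized. The abstract puts city differences into subgroup analyses, and the primary objective covers both cities together. Moreover, if each city carried its own separate claim, the relevant error for that claim would be the two-visit figure. The four-test range applies only if success in any city at any visit counts as one trial-level win. This objection stands, and the 14–19% is therefore conditional.

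2. **The threshold is stated for the primary outcome in the singular, so an either-visit rule is not written down.** This is also true. It would be wrong to say that 0.05 fails under every reading, because a both-visits rule would control the error. But that rule is not written down either, and within a city it does not deliver the stated 80% power.

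3. **The power loss disappears on pooling.** This is correct. With 97.6% power at each visit, power for both is at least 1 − 2 × 2.4% = 95.2% whatever the correlation. The shortfall in Step 3 belongs to the per-city reading, which is the basis on which the protocol states its power.

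4. **A journal article may leave multiplicity to an analysis plan that is not shown.** The absence of a detailed procedure is indeed no finding by itself. The point rests on what the article does fix: two primary visits, t-tests at both time points, a bare 0.05, a sample size for one test, and two different roles for city.

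**Conclusion.** The point holds in a bounded form. Two unranked primary visits share one unadjusted two-sided 0.05. If either suffices, the false-positive risk is about 7–10%, not 5%, for r from 0.9 to 0. A single figure such as 9% would rest on an assumed r near 0.5, which the document does not supply. The 14–19% for two cities needs two further assumptions, separate primary tests per city and success in any of them, and the text leans against the first. If both visits are required, error is controlled, but per-city power is about 64–75% on the protocol's own difference and SD.

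So, at the level of a single city, no reading that keeps both visits primary with an unadjusted 0.05 gives both a 5% error and the stated 80% power. This affects what the trial may conclude, so it should be settled before any outcome data are seen.

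**What to change.** - State that the primary analysis is one comparison of the arms, pooled over cities and adjusted for city.
- Either name one visit as primary, or test the two visits in a prespecified fixed order, each at two-sided 0.05, with the second tested only if the first is significant. The order is the sponsor's choice, made before seeing data. Postnatal first is one option, since the sample-size section justifies the 20% difference by postpartum depression. The 34–36 week visit is also defensible, because it lies closer to the support sessions.
- Report city-specific effects with confidence intervals and an arm-by-city interaction as secondary results, and apply the same rule to any added city.
- Bring the sample-size wording on alpha in each location into line with this.

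**Cost:** wording only, with no extra women. In a fixed order, the second visit can be claimed only if the first succeeds, and no city-level primary claim is made. Power for a single pooled test, or for the first test in the order, is about 97.6% with 80 evaluable per arm, a difference of 2.5 and an SD of 4.0.

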#### Psychological assessments

EPDS^41 42^ is a widely validated screening instrument. A high EPDS score does not in itself confirm a diagnosis of depression. A score above a certain cut-off point may, however, indicate probable depressive disorder. In the present study, the EPDS will be administered in the third trimester of pregnancy (a 34–36 weeks) and at 4–6 weeks postpartum. An EPDS cut-off score of >10 has been found to be optimal for perinatal screening for depression.^43^

*The* GAD7 questionnaire^44 45^ has been translated into Chinese and validated in general hospital outpatients, with a cut-off score of >10^22^ to indicate anxiety.

IES-R will be used to assess PTSD. It has been translated and validated in Chinese^46–48^ to assess symptoms of PTSD corresponding with Diagnostic and Statistical Manual of Mental Disorders (DSM-V).^46 47^ A survey about COVID-19 will also be administered at the same time points (at 34–36 weeks of gestation and 4–6 weeks postpartum).

The EPDS, GAD7 and IES-R scales were chosen over psychodiagnositc interviews because they show high reliability and validity and are more cost-effective and efficient compared with psychodiagnostic interviews.^49^

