## Material and methods

### Trial design and setting

The Mental health of Urban Mothers trial is a prospective randomised controlled trial that will be performed in order to assess the effects of psychosocial support during pregnancy that focuses on factors that can reduce mental health problems and adverse outcomes in pregnant and postpartum women (intervention) versus standard care (control group). The intervention will be delivered by trained peers. Participating women will be recruited from two large urban areas, that is, Hong Kong (7.5 million inhabitants and among all maternity hospitals 11 027 annual deliveries^36^ and Shanghai (25 million inhabitants and Shanghai Maternity and Child Healthcare Hospital with more than117 700 deliveries per year). The intervention group will receive web-based psychosocial peer-to-peer support two times during the antenatal period before 36 gestational weeks (at 18–22 weeks and 24–28 weeks) and the control group will receive the usual standard antenatal care. Mental health status will be assessed using standard questionnaires, that is, EPDS and GAD7 and IES-R. Information on the course and outcome of pregnancy will be obtained by sending a questionnaire at 4–6 weeks postnatally via a web survey.

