### Recruitment and blinding

Pregnant women will be recruited via non-profit organisation websites in each country. In addition to Hong Kong and Shanghai, we aim to include additional urban locations, including Stockholm, Sweden in this multicenter study. Via web link, the women will be guided to the research project website. The peer support website includes information about the project and informed consent. By completing the initial sociodemographic survey, the women can consent to participate in the research study. Then, they will ask to use an app to follow the study and complete the survey questionnaires. The participating women will be automatically randomised to intervention (peer-to-peer web-based psychosocial support) or control group (standard care) by the computer-generated random sequence. Regardless of recruitment to the intervention or control group, the women will continue their regular visits at the maternity clinics as usual.

Both the women and their peers will be forbidden to inform anyone in the study about which study group they belonged to. However, due to the nature of intervention, investigators, as well as the study participants, will not be blinded to the intervention.

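### The text schedules no EPDS before the intervention, so the primary analysis cannot use baseline severity and the imputation model lacks its main predictor for the 34–36 week score

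*Protocol article*

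**What the plan says.** All places are in the protocol article.

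- **Assessments.** Outcome measures: "The primary outcome measure is the woman’s EPDS assessed at 34–36 weeks of gestation and at 4–6 weeks postnatally". Psychological assessments repeats the same two time points: "the EPDS will be administered in the third trimester of pregnancy (a 34–36 weeks) and at 4–6 weeks postpartum".
- **Intervention.** Under Trial design and setting, support is given "two times during the antenatal period before 36 gestational weeks (at 18–22 weeks and 24–28 weeks", so both contacts precede the first EPDS.
- **Entry.** Inclusion criteria: "Pregnant women between 12 and 18 weeks of gestation with viable intrauterine pregnancy". Recruitment and blinding: "By completing the initial sociodemographic survey, the women can consent to participate in the research study". Automatic randomisation is described after this survey.
- **Analysis.** Statistical methods: "Average EPDS, GAD7 and IES-R scores will be compared between the intervention and control groups and across time points (prenatal and postnatal), using independent sample"; the test named is the unpaired t-test. No covariate is named.
- **Imputation.** Statistical methods: "The variables used in the imputation mode will be previous EPDS score, education level and parity".
- **Subgroups.** Statistical methods also announces analyses by several EPDS score groups, without saying which assessment defines them.
- **Sample size.** The trial is sized "to detect a 20% difference in mean EPDS scores between the intervention versus control groups" in each location, with mean 12.5, SD 4.0, 80% power, alpha 0.05, 40 women per arm per city, and 100 per city after allowing for dropout.

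**The concern.** The scale that carries the primary outcome is, on the text, first measured after the intervention has ended. Three things follow.

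1. **Precision.** With 40 evaluable women per arm in each city, differences between arms in depressive symptoms at entry can be neither seen nor adjusted for. The list under Confounders does not include them. Power is close to 80% with nothing in reserve.
2. **Imputation.** The model names an earlier EPDS as a predictor. For the first of the two primary time points the text provides none.
3. **Subgroups.** If the EPDS subgroups are meant as severity subgroups, they could be formed only on a score taken after randomisation, which the intervention may have changed.

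An online survey is already completed at entry, so the opportunity to collect the score exists.

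**Working it through.** **Inputs from the protocol article (Sample size and power calculation; Statistical methods):** difference 20% × 12.5 = 2.5 points; SD 4.0; two-sided alpha 0.05; 40 per arm per city.

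**Assumption, not in the documents:** correlation r between enrolment EPDS and outcome EPDS, shown for 0.3, 0.5 and 0.7.

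**Step 1. Reproduce the stated size.** Standardised effect = 2.5/4.0 = 0.625. The normal formula gives n = 2 × (1.960 + 0.842)² × 4.0² / 2.5² = 40.2 per arm, that is 41 rounded up, against the stated 40. Power at 40 per arm is 79.8% (normal) or 78.8% (noncentral t). The stated figure reproduces. The step from 80 to 100 per city corresponds to 20% loss (80/0.8 = 100).

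**Step 2. Effect of a baseline covariate, per city.** ANCOVA multiplies the outcome variance by (1 − r²), so the effect becomes 0.625/√(1 − r²), and 40 women act like 40/(1 − r²).

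| r | effect | power at 40 per arm (noncentral t) | equivalent unadjusted n per arm |
|---|---|---|---|
| none | 0.625 | 78.8% | 40 |
| 0.3 | 0.655 | 82.5% | 44 |
| 0.5 | 0.722 | 89.0% | 53 |
| 0.7 | 0.875 | 97.2% | 78 |

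The gain needs the change of analysis: a baseline collected but left out of an unadjusted t-test adds nothing. Change scores are a poorer use of it. Their variance factor is 2(1 − r), so by the normal formula they need 57, 41 or 25 per arm at r = 0.3, 0.5 or 0.7, against 37, 31 or 21 for ANCOVA.

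**Step 3. Pooled over two cities.** With 80 per arm, power is 97.6% unadjusted and 99.5% at r = 0.5.

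**Step 4. Which missing scores have an earlier EPDS?**

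| Missing | Earlier EPDS on the text |
|---|---|
| 4–6 weeks postnatal only | yes, the 34–36 week score |
| 34–36 weeks only | none |
| both | none |

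The stated model thus works for a woman who misses only the postnatal assessment. For women lost before 34–36 weeks it is left with education and parity.

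**The case against.** **A baseline may exist.** Figure 1 is the study timeline, and its legend defines EPDS, GAD7 and IES-R. The imputation sentence refers to an earlier EPDS, and the last sentence of Statistical methods places antenatal scores before 34–36 weeks by a less-than sign. A reader might still infer that the scale is certainly never measured at entry. The documents do not support that: what can be said is that the text schedules none. If the figure shows one, it conflicts with Outcome measures and Psychological assessments, and the primary analysis as described does not use it, although covariates may be specified in an analysis plan that is not shown.

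**The design is valid without it.** This stands. Under randomisation the unadjusted comparison of follow-up scores is unbiased, chance imbalance is already covered by the test's error rate, and the stated sample size is essentially met. A reader might conclude that the trial is biased or underpowered for want of a baseline; the figures do not support that.

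**The imputation is not impossible.** This also stands: it works for a missing postnatal score when the 34–36 week score is present.

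**The subgroup harm is inferred.** Correct. The article does not say the subgroups are by severity at entry, and the cut-offs above 10 and above 15 in the Analysis plan are outcome categories. The point applies only if severity subgroups are intended.

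**The power gain depends on the analysis and on r.** The figures in Step 2 are for separate city analyses, which is how the trial is sized. In a pooled analysis little is gained. At r = 0.3 the per-city gain is under 4 percentage points. Enrolment at 12–18 weeks precedes the first outcome by 16 to 24 weeks, so 0.7 may be optimistic.

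**Conclusion.** The point holds as a recommended improvement. On the text, no EPDS precedes the intervention. The primary t-test therefore cannot use baseline severity, and the imputation model lacks its EPDS predictor for missing 34–36 week scores and for women with no EPDS.

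For the per-city analysis, baseline adjustment would raise power from 79% to between about 82% and 97%. This rests on the protocol's own difference and SD, on 40 evaluable women per arm, and on an assumed correlation of 0.3 to 0.7. It does not invalidate the comparison or the sample size. The conclusion that no baseline exists is conditional on Figure 1.

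**What to change.** 1. Add the EPDS, and the GAD7, to the enrolment web survey, completed before randomisation. If Figure 1 already shows a baseline EPDS, reconcile Outcome measures and Psychological assessments with it instead.
2. Analyse the primary outcome by ANCOVA with enrolment EPDS as covariate within each city. Add city as a covariate only in a pooled analysis.
3. Name enrolment EPDS explicitly in the imputation model for both time points.
4. State what the EPDS subgroups are. Base any severity subgroup on enrolment EPDS, not on a score taken after randomisation.

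**Cost.** A short amendment and slightly more burden in a survey that women already complete. High scores become visible at entry, and the trial's procedures must cover them; the same scale already makes them visible later in the trial. Women already enrolled will have no baseline, and the analysis must say how they are handled, for example with a missing-baseline indicator.
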